### Randomization procedure

Using a double-blind procedure, we will randomly assign all of the participants to one of the four groups. The randomization scheme will be generated using the website Randomization.com (http://www.randomization.com). Randomization and follow-up assessments will be administered by independent practitioners blind to the research hypotheses and condition assignments. The G*Power software (v3.1.9.2) [35, 36] was used to compute the minimum sample size required to conduct this study. All of the participants will be assessed with the Psychological General Well-Being Index (PGWBI) [47, 62, 85] five times: (1) at admission to the clinic, (2) at discharge, (3) at 3 months follow-up, (4) at 6 months follow-up, and (5) at 12 months follow-up. Thus, the *experimental condition* is considered as a between-group variable, and *time* is considered as a within-subject variable. The a priori statistics (partial η^2^ and correlation between measures) were computed by examining previous longitudinal studies using the PGWBI in subjects with obesity [9, 65]. The a priori partial η^2^ was set to assume a value of 0.015 (small effect size) [26, 30], the type I error (α) rate was set at 0.05 (two-sided), the power (1 – β) was set at 0.95 [26], and the a priori correlation between repeated measures was set at 0.50. Finally, sphericity was assumed. G*Power showed that there is a 95% chance to correctly reject the null hypothesis of no significant effect with an overall sample of 168 participants, 42 subjects for each group.

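### If the partial η² of 0.015 is a repeated-measures ANOVA value, the sample-size calculation counts the visit correlation twice, and power at 168 is about 50%, not 95%

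*Protocol article*

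**What the plan says.** The sample-size calculation is in the Randomization procedure section of the protocol article. It treats experimental condition (four groups) as the between-group factor and time as the within-subject factor. The PGWBI is measured "five times: (1) at admission to the clinic, (2) at discharge, (3) at 3 months follow-up, (4) at 6 months follow-up" and finally at 12 months.

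The inputs are:
- Effect size: "The a priori partial η^2^ was set to assume a value of 0.015 (small effect size".
- Error rate and power: "the type I error (α) rate was set at 0.05 (two-sided") and "the power (1 – β) was set at 0.95".
- Correlation: "the a priori correlation between repeated measures was set at 0.50".
- Covariance: "Finally, sphericity was assumed".

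On the origin of two of these inputs it says: "The a priori statistics (partial η^2^ and correlation between measures) were computed by examining previous longitudinal studies using the PGWBI in subjects with obesity". The result is a 95% chance of rejecting the null hypothesis "with an overall sample of 168 participants, 42 subjects for each group". The article names the G*Power version. It does not say which of the program's effect-size definitions was used, or whether 0.015 was converted from one scale to another.

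**The concern.** A partial η² for a group-by-time interaction can mean two different things.

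- **ANOVA scale.** This is the value that a repeated-measures ANOVA reports: the interaction sum of squares divided by itself plus the within-subject error sum of squares. A higher correlation between visits shrinks that error, so the correlation is already in the value.
- **Raw-score SD scale.** Here the effect is set against the ordinary between-person SD at a single visit. The correlation is not in the value and has to be supplied separately.

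G*Power's default option expects the second kind and divides by (1−ρ). A value of the first kind entered there uses the correlation twice and overstates the power. An effect size obtained from longitudinal studies, with no conversion reported, is most naturally of the first kind.

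The 95% figure is the article's only quantitative justification for 168 participants. If the real figure is about one in two for the effect that those studies suggest, a non-significant PGWBI interaction says far less than the stated power implies.

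**Working it through.** **Inputs** (all from the Randomization procedure section): k = 4 groups, m = 5 visits, N = 168, α = 0.05, ρ = 0.50, sphericity, partial η² = 0.015.

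f² = η²/(1−η²) = 0.015/0.985 = 0.01523, so f = 0.1234.

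Interaction degrees of freedom: df1 = (k−1)(m−1) = 3 × 4 = 12; df2 = (N−k)(m−1) = 164 × 4 = 656. Power is the upper tail of the noncentral F distribution beyond the 5% critical value.

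**Step 1. Reproduce the stated figure (default scaling).**

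λ = N·m·f²/(1−ρ) = 168 × 5 × 0.01523/0.5 = 25.58, which gives power 94.4%. The printed 0.015 is rounded: η² = 0.0154 (f = 0.125) gives λ = 26.25 and 95.0% at N = 168. The stated result is therefore reproduced within the precision of its input.

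**Step 2. Check that no other reading gives 95%.** Same N and η²:

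| Test and scaling | Power |
|---|---|
| Interaction, default scaling, ρ = 0.5 | 94.4% |
| Interaction, same scaling, ρ = 0 (λ = 12.79) | 62.7% |
| Group main effect | 37.2% |
| Time main effect | 99.0% |
| Interaction with two groups | 99.0% |

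Of the readings tried, only the first matches. The effect-size option is thus inferred from the match; the article does not name it.

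**Step 3. Take 0.015 as the repeated-measures ANOVA value.**

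λ = f²·(N−k)(m−1) = 0.01523 × 164 × 4 = 9.99, with no further use of ρ. Power is 49.6%. Using N instead of N−k gives λ = 10.23 and 50.8%, so the choice between them does not matter.

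**Step 4. Explain the gap.** The ratio of the two noncentralities is 25.58/9.99 = 2.56. It factors as m/[(m−1)(1−ρ)] × N/(N−k) = 5/(4 × 0.5) × 168/164 = 2.5 × 1.024. A factor of 2 comes from the second use of the correlation, and the rest from m against m−1 and N against N−k.

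Equivalently, 0.015 on the raw-score scale corresponds to an ANOVA-scale f² of 0.01523 × 2.5 = 0.0381, a partial η² of about 0.037.

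**Step 5. What 168 can detect, and what 0.015 would need, on the ANOVA scale.** Power of 95% at N = 168 requires a partial η² of 0.0385 (f² = 0.0385/0.9615 = 0.0400; λ = 0.0400 × 656, about 26.3). To detect 0.015 would take about 432 participants for 95% power and about 292 for 80%. These numbers show the size of the gap; they are not a proposal to enlarge the trial.

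**Step 6. Simulation check.** Simulating the 4 × 5 design (42 per group, equal correlation 0.5, 4000 runs) gave 94.1% with the effect set on the raw-score scale and 50.2% with it set as an ANOVA partial η² of 0.015.

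**The case against.** The strongest reply is that the double count is not shown in the text. The article says that the values were obtained by examining studies, not that they were reported in them, so 0.015 could have been worked out from published means and SDs. That would put it on the raw-score scale. The value carries a size label and its own references, distinct from those given for the PGWBI studies, which could point to a benchmark. The correlation was collected as a separate input, which is what the default option requires. On any of these readings ρ enters once, correctly. This reply stands in part: the scale cannot be settled without the cited sources, so the point has to remain conditional. It does not remove the point, because the article's only account of where 0.015 came from is longitudinal studies, and no conversion is reported.

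A reader might infer several stronger things that the document does not support:

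- **That the stated 95% is proven wrong.** It is wrong only if 0.015 is the ANOVA value.
- **That 168 falls short even on the favourable scale**, because the exact calculation gives 94.4%. That is rounding of the printed effect size.
- **That assuming sphericity is a further error.** It is a declared planning assumption. The Statistical analysis section provides for assumption checks and robust methods, and the article gives no figure from which to quantify a departure.
- **That the primary outcome is underpowered.** The calculation is for the PGWBI, whereas the sections on hypotheses and assessment make tracker-measured physical activity primary. This calculation says nothing about power for that outcome.

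The risk of misreading a null result is also softened. The Discussion concedes that the subgroups are small, and the Statistical analysis section plans effect sizes with 95% confidence intervals.

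**Conclusion.** The point holds in conditional form. The stated 168 for 95% power matches G*Power's default scaling for the group-by-time interaction. If 0.015 is a repeated-measures ANOVA partial η², which is the natural reading of the text, the correlation is counted twice. Power at 168 is then about 50%, and 95% power is available only for a partial η² of about 0.039, some 2.6 times the stated value. If 0.015 is on the raw-score SD scale, the stated 95% stands within rounding.

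The conclusion rests on two things that the article does not state: the effect-size option, inferred because it alone reproduced the result, and the scale of 0.015, inferred from its described origin. The figure supports the PGWBI comparison only. It is worth correcting, because the article makes a definite power claim and rests the sample size on it, but it does not affect the conduct of the trial.

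**What to change.** Keep N at 168. Go back to the source of 0.015 and establish its scale, then amend the sample-size text in the Randomization procedure section:

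- **If it is the repeated-measures ANOVA value:** rerun the calculation with the effect-size option that matches that definition. Then either restate the power at 168 as about 50% for a partial η² of 0.015, or give about 0.039 as the effect detectable with 95% power.
- **If it is on the raw-score SD scale:** say so and name the option used. The stated 95% can then remain.

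In either case, say that the calculation is for the group-by-time interaction on the PGWBI. The cost is a few sentences and, in the first case, a less favourable power statement. No participants, visits or procedures change.

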### Statistical analysis

As this study combines group design with different single-case design or, more in detail, randomly assigned multiple baseline design clustered by sub-sequential recruitment. Following methodological guidelines of RCT, the implementation of statistical analysis is linked to synergies that we can not previse at this point.

Statistical analyses will be performed using the R software [86]. Preliminary analyses will be carried out to assess the assumptions of parametric statistics; in case of violations, robust methods or data transformation will be used. Direct collected data (steps, weight, etc.) will be analyzed with an ITT approach with dropouts assumed to have regained 0.3 kg per month, an assumption already used in previous studies [16]. Dropouts will be excluded from the study.

The analysis of variance (ANOVA) will be used to examine between-group differences for all the primary and secondary outcomes at all time-points, focusing on the change in the scores. Corrected effect sizes (Hedges’ *g*) and 95% confidence interval (95% CI) will be calculated for both between-group and within-group differences.

Moreover, growth curve model analysis with a group variable (between conditions) will be used to evaluate the average growth from the baseline to 12 months after treatment for all of the outcome variables as performed in previous studies [52]. Moderation and meditational analysis will be implemented as more advanced statistical models. All data analyses will be performed using the Statistical Package for the Social Sciences (version 16.0; SPSS, Inc., Chicago, IL).

In addition, considering that the present study combines different single-case designs, more detailed randomly assigned multiple baseline designs clustered by sub-sequential recruitment, and a group design following methodological guidelines of RCTs, the implementation of statistical analysis is linked to synergies that we cannot previse at this point. For the single-case design, we use a multiple-baseline procedure with the same number of data points for all the subjects assigned to a cluster. In each multiple-baseline cluster we randomly assign the length of the baseline and, consequently, of the treatment. Detailed visual inspection and graphical analysis will be use, followed by a randomization test to ensure statistical power to the visual analysis [37, 38].

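### The 95% power is stated for an effect labelled small, but in the calculation that yields 168 participants the input 0.015 corresponds to a largest arm difference of about 0.5 to 1.0 SD

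*Protocol article*

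**What the plan says.** The sample size is derived in the protocol article under Methods, Randomization procedure. The outcome is the PGWBI, measured five times (admission, discharge, 3, 6 and 12 months). Condition is the between-group factor and time the within-subject factor.

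The a priori partial η² "was set to assume a value of 0.015 (small effect size"). It and the correlation are said to come from earlier longitudinal PGWBI studies in obesity. The other inputs are: "the type I error (α) rate was set at 0.05 (two-sided"), "the power (1 – β) was set at 0.95", "the a priori correlation between repeated measures was set at 0.50", and "Finally, sphericity was assumed".

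The conclusion is: "G*Power showed that there is a 95% chance to correctly reject the null hypothesis of no significant effect with an overall sample of 168 participants", with 42 in each arm. The paragraph does not say which effect is tested (group, time, or group by time) or which G*Power effect-size option was used. It gives no detectable difference in PGWBI points or SDs.

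Under Statistical analysis, results are to be reported as Hedges' g with 95% confidence intervals, which "will be calculated for both between-group and within-group differences".

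**The concern.** Read at face value, the paragraph promises a 95% chance of detecting a small effect. Readers of the results will see standardised differences between arms, and will naturally carry the word small over to that scale. In a four-arm, five-visit interaction the two scales are far apart. G*Power's f² is then the interaction variance averaged over 20 arm-by-visit cells, after the arm and visit main effects have been removed. Randomised arms are expected to be equal at admission, and part of any sustained arm difference goes into the arm main effect. The arms must therefore separate substantially at follow-up before the averaged interaction reaches 0.015.

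If the label stays, a non-significant group-by-time test could be taken as good evidence against small benefits of ACT or feedback. The design does not supply that evidence.

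**Working it through.** **Inputs (all from Randomization procedure):** k = 4 groups, m = 5 visits, N = 168 (n = 42 per arm), ρ = 0.50, sphericity (ε = 1), α = 0.05, partial η² = 0.015.

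**1. Reproducing the plan's figure.** For the group-by-time interaction under the default scaling:

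- f² = 0.015 / 0.985 = 0.01523, so f = 0.1234
- λ = N·m·f² / (1 − ρ) = 168 × 5 × 0.01523 / 0.5 = 25.58
- df = (k − 1)(m − 1) = 12 and (N − k)(m − 1) = 656
- Power from the noncentral F = 0.944 (0.950 with f rounded to 0.125)

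The minimum N for 95% power is 173 at exactly 0.015, and 168 at 0.0154, which rounds to 0.015. The plan's figure is therefore reproduced within rounding. The other candidates do not reproduce it:

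| Test | Power at N = 168 | N for 95% power |
|---|---|---|
| Interaction, default option | 0.944 | 173 |
| Between-group effect | 0.37 | 684 |
| Time effect | 0.99 | 124 |
| Interaction, SPSS-type option | 0.50 | about 430 |
| Interaction, Cohen-type option | 0.13 | 1704 |

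**2. Translating 0.015 into arm differences.** Let the arm means follow d × (arm pattern) × (time pattern), with d the largest arm difference in per-visit SDs, each pattern scaled to a maximum of 1, and no difference at admission. The 20 squared interaction effects sum to 20·d²·Var(arm)·Var(time), so

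λ = 42 × 20 × d² × Var(arm) × Var(time) / 0.5 = 1680 × d² × Var(arm) × Var(time).

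Setting λ = 25.58 and solving for d:

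| Arm pattern | Time pattern | Var(arm) | Var(time) | d for the plan's λ | Power at d = 0.2 | Power at d = 0.3 |
|---|---|---|---|---|---|---|
| One factor works (0,0,1,1) | from 3 months (0,0,1,1,1) | 0.25 | 0.24 | 0.504 | 0.196 | 0.450 |
| One factor works | from discharge (0,1,1,1,1) | 0.25 | 0.16 | 0.617 | 0.139 | 0.294 |
| Factors add (0,½,½,1) | from 3 months | 0.125 | 0.24 | 0.712 | 0.113 | 0.220 |
| Factors add | from discharge | 0.125 | 0.16 | 0.873 | 0.089 | 0.152 |
| Factors add | equal steps over visits | 0.125 | 0.125 | 0.987 | 0.080 | 0.126 |

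Over 28 non-crossing patterns (4 arm shapes × 7 time shapes), d runs from 0.50 to 0.99 SD. Power at 0.2 SD is 8% to 20%, at 0.3 SD 13% to 45%, and at 0.5 SD 32% to 94%. Simulation of the two extreme rows gave power of 0.948 at 0.504 SD and 0.946 at 0.987 SD; at 0.2 SD it gave 0.196 and 0.078.

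When the factors add, d is the gap between the combined and control arms. Each factor contributes half: 0.712/2 = 0.36 SD to 0.987/2 = 0.49 SD.

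**3. Link to Hedges' g.** The SD of a change score is √[2(1 − ρ)] = √1 = 1 per-visit SD at ρ = 0.50. These values of d are therefore also on the scale of a g computed on change scores.

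**4. If 0.015 is an ordinary published partial η².** Then λ = f² × 656 = 0.01523 × 656 = 9.99 and power at 168 is 0.50. In the other direction, λ = 25.58 corresponds to a partial η² of 25.58 / (25.58 + 656) = 0.0375. With N(m − 1) = 672 in place of 656 it is 0.0367, so about 0.037. On this reading 0.015 means a largest gap of about 0.31 to 0.62 SD.

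**5. A more focused test.** Take the mean of the four later visits minus admission, with a constant effect: SD = √(0.625 + 1 − 2 × 0.5) = 0.79. Power at 0.2 SD is 37% for 84 v 84 and 21% for 42 v 42. With baseline adjustment instead, SD = √(0.625 − 0.25) = 0.61 and power for 84 v 84 is 56%.

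**The case against.** The strongest reply is that nothing was miscalculated. The inputs give 168 within rounding, and the label is attached to partial η², on which 0.015 is small by the usual convention. The article nowhere claims power for a small difference in SDs, and taking small as 0.2 SD is a benchmark from outside it. All of that stands. A reader might infer a faulty sample size calculation, and the documents do not support that.

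A reader might also infer that the trial has almost no power for small differences in any analysis. That goes too far. The 8% to 20% belongs to the 12-df omnibus interaction. The article describes a 2 × 2 factorial and plans ANOVA on change and growth curves, and a focused 84 v 84 comparison reaches roughly 37% to 56% at 0.2 SD. This is better, but still well below 95%.

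Nor do the 0.87 and 0.99 SD figures mean that ACT or feedback alone must have so large an effect. They are combined-versus-control gaps.

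Finally, the article plans confidence intervals, calls itself a small RCT under Study design, and concedes small subgroups in the Discussion. These limit the risk of over-reading a null result. They do not correct the sentence that pairs 95% power with a small effect.

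**Conclusion.** The point holds as a misstatement of sensitivity, not as an arithmetic error. Of the tests checked, only the group-by-time interaction under the default scaling yields the printed 168 and 95%. There, 0.015 corresponds to a largest arm difference of about 0.50 to 0.99 SD, and the same test has at most about 20% power at 0.2 SD and 45% at 0.3 SD. If 0.015 is an ordinary partial η², as its stated source in earlier studies suggests, 95% fails on the plan's own scale as well: power is about 50%. The article does not show which reading was meant, but on neither does 95% power extend to small between-arm differences.

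The SD figures assume equal arms at admission, profiles that do not cross, correlation 0.50, sphericity and complete data. Profiles that reverse over time would need smaller differences. A wording change should be made; the sample size need not change on this account.

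**What to change.** In the sample size paragraph under Randomization procedure, name the tested effect (group by time) and the G*Power effect-size option, delete the parenthetical label after 0.015, and restate the sensitivity at the same N. For example:

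> With 42 per group and complete data, the group-by-time test has about 95% power for an ordinary partial η² of about 0.037, equivalent to a largest arm difference of about 0.5 to 1.0 SD depending on the pattern (equal baselines, non-crossing profiles, correlation 0.50). Power of this test for a 0.2 SD difference is at most about 20%, so a non-significant result does not exclude small effects.

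The cost is a sentence or two of text and a less favourable statement of what the trial can detect. It needs no extra participants, visits or procedures.

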
### The present study

Principal reasons for the long-term failure of obesity interventions are the lack of long-term sources of reinforcement for healthful habits acquired during the intensive treatment period [14, 31, 32]. The tradition of behavioral sciences has developed models of interpretation, explanation, and pragmatic operation supported by evidence of effectiveness and efficiency in the promotion of desired behaviors in various contexts, for example, smoke cessation [10, 81], pathological Internet use [69, 70], the ability to live with chronic diseases [6, 48, 66], and the promotion of safety behaviors in working environments [71, 88]. For this reason, behavior analysis in general, and in particular *contextual behavioral science*, can play a decisive role in the prevention of obesity and in the maintenance of the results achieved within short intensive protocols, usually held in hospitals. By modifying deeply rooted and long-term acquired habits, obese patients can obtain more psychological and physical health, reduce risk factors, and improve their overall health, wellness, and quality of life [53, 59] with benefits not only for the individual but also for his social environment. During rehabilitation patients affected by obesity are frequently in contact with contingencies extremely different from those occurring in their daily lives. During rehabilitation or hospitalization, contingencies are efficiently shaped to promote desired behaviors and decrease actions that are identified as dysfunctional, with both aversive and reinforcing contingencies. Later on, after the treatment, in the patient’s natural environment initially behaviors are maintained, but since they were reinforced in an environment that provides adequate contingencies, they often undergo a process of extinction consequently with cessation of reinforcement [79]. At the same time, outside the hospital, dysfunctional behaviors, such as avoiding physical activity and eating tasty food, are reinforced in a systematic and contingent way. This tendency to extinction of functional and healthful habits and reinforcement of dysfunctional habits leads, in the long term, to gaining of the weight lost laboriously, which also leads to lower levels of well-being [77]. Although the existing programs already provide protocol phases to be implemented once patients are home, often the patients fail to adhere to nutrition programs and planned activities. On the contrary, they return frequently to previous habits and show a high dropout rate at follow-ups [76].

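### The stated 95% power for the PGWBI is a complete-data figure with no reserve for dropout, while the analysis section says both that dropouts are excluded and that analysis is by intention to treat

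*Protocol article*

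**What the plan says.** The Randomization procedure section of the protocol article holds the sample size calculation. It is built on the PGWBI, assessed at admission, discharge, 3, 6 and 12 months, with condition as the between-group factor and time as the within-subject factor. The inputs are a partial η² of 0.015 and a two-sided α of 0.05; "the power (1 – β) was set at 0.95"; "the a priori correlation between repeated measures was set at 0.50"; and "Finally, sphericity was assumed". The result is that "G*Power showed that there is a 95% chance to correctly reject the null hypothesis of no significant effect with an overall sample of 168 participants", in four groups of 42. The section calls this a minimum and lists no step for dropout.

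On dropouts, the Statistical analysis section makes two statements in succession. The first is that directly collected data such as steps and weight are analysed by intention to treat (ITT), with dropouts assumed to regain 0.3 kg per month. The second is: "Dropouts will be excluded from the study". The Study design section also declares ITT. The Statistical analysis section further plans a growth curve model from baseline to 12 months for all outcomes.

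In the background (The present study), the article says that patients in existing programs "show a high dropout rate at follow-ups".

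**The concern.** A repeated-measures ANOVA calculation with five assessments counts people who supply all five. If the same 168 are the people randomised, and those who leave are then removed, the number analysed is below the number on which the 95% rests. The article's own background gives reason to expect some loss by 12 months.

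At stake is how a null PGWBI result is read. A reader told that the chance of missing the assumed effect is 5% would give such a result more weight than the design supports. The ITT contradiction makes this worse, because the reader cannot tell which participants the power figure describes.

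**Working it through.** **Inputs, all from the Randomization procedure section**
- Groups k = 4; assessments m = 5; N = 168
- Partial η² = 0.015, so f² = 0.015/0.985 = 0.01523 and f = 0.1234
- Correlation ρ = 0.50; sphericity, so ε = 1; α = 0.05

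**Step 1. Reproduce the plan's figure.** The article does not name the G*Power test. The within-between (group-by-time) interaction with the default effect-size option uses:
- λ = f² × N × m/(1 − ρ)
- df1 = (k − 1)(m − 1) = 3 × 4 = 12
- df2 = (N − k)(m − 1) = 164 × 4 = 656

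λ = 0.01523 × 168 × 5/0.5 = 25.6. The noncentral F distribution gives power 0.944. With f rounded to 0.125, f² = 0.015625, λ = 26.25 and power is 0.950. With unrounded f the smallest N that reaches 0.95 is 173, which is 3.0% above 168. The stated figure is therefore reproduced within rounding.

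Other choices do not reproduce it. At N = 168 the time main effect has power 0.990 and would need 124. The between-group main effect has power 0.372 and would need 681. The interaction with the SPSS-type or Cohen-type effect-size option has power of about 0.50 to 0.51 and would need 432 or 428. So 168 is the complete-data number for the default interaction test, with no hidden margin. The rest of this check takes that test and its scaling as given.

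**Step 2. Remove dropouts.** The article gives no dropout rate, so the range below is an assumption. Completers = 168 × (1 − d), rounded to the nearest whole number; df2 = 4 × (completers − 4).

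| Assumed dropout d | Completers | λ (f = 0.1234) | Power (f = 0.1234) | Power (f = 0.125) |
|---|---|---|---|---|
| 0% | 168 | 25.6 | 0.944 | 0.950 |
| 10% | 151 | 23.0 | 0.912 | 0.92 |
| 20% | 134 | 20.4 | 0.866 | 0.88 |
| 30% | 118 | 18.0 | 0.806 | 0.82 |
| 40% | 101 | 15.4 | 0.723 | 0.74 |

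At 5% dropout (159 completers) power is 0.928.

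**Step 3. Type II error.** With f = 0.1234 it is 1 − 0.944 = 0.056 with nobody lost, 1 − 0.866 = 0.134 at 20% and 1 − 0.806 = 0.194 at 30%. The ratios are 0.134/0.056 ≈ 2.4 and 0.194/0.056 ≈ 3.5.

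**Step 4. Does the ITT rule restore the lost participants?** A regain of 0.3 kg per month yields a weight. It does not yield a PGWBI score, which is the powered outcome, or a step count, which belongs to the primary outcome. For those two the article offers no rule other than exclusion.

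**The case against.** **168 may mean the number needed for analysis.** The article calls it a minimum, the text shown gives no separate recruitment target, and the flow diagram and schedule figures are not available here. This has some force. It is why one acceptable repair is simply to say that 168 means completers. But the article also calls 168 the overall sample, splits it into the four groups and mentions no larger number.

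**Exclusion is not clearly the settled rule.** This stands. ITT is stated in two sections, and a growth curve model can use partial data, which would soften the loss. So the losses in the table apply to the exclusion sentence as written, and are not inevitable.

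**The dropout remark concerns other programs.** Also true. A reader might infer that the article forecasts high dropout in this trial. It does not: the remark is background on existing programs and gives no rate.

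**The calculation reproduces, and power remains respectable.** Both are correct. A reader might infer that the sample size was miscalculated or that the trial is underpowered. Neither follows: 168 reproduces within rounding, and power stays at about 0.80 or more up to roughly 30% dropout.

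**The 95% is not the trial's sensitivity for its main question.** A reader might take it as the chance of detecting an effect on the primary outcome. The documents do not support that. The calculation concerns the PGWBI, the primary outcome is tracker-measured physical activity (Assessment procedure), and the article states no power for it. The planned Hedges' g with 95% confidence intervals would also show directly how imprecise a null result is.

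**Conclusion.** The point holds in a limited form. The 95% is the complete-data power for the PGWBI group-by-time interaction. The design as described does not deliver it if participants leave over 12 months and are excluded. Power would be about 0.91, 0.87, 0.81 and 0.72 at 10%, 20%, 30% and 40% dropout, a moderate loss over most of that range.

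This rests on four assumptions: the default G*Power interaction test was used, which is inferred because it alone reproduces 168; the effect size, correlation and sphericity are as stated; 168 is the number randomised; and the dropout rates are mine. It also takes the exclusion sentence at its word, although the ITT statements contradict it. That contradiction is itself a defect to resolve.

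**What to change.** 1. Reconcile the ITT and exclusion sentences. Delete the exclusion and state that all randomised participants are kept, with their available data, in the growth curve model already planned. Say that the 0.3 kg per month rule applies to weight only.
2. State an expected 12-month dropout rate and restate the power for the number expected to remain, for example about 87% at 20% dropout and 81% at 30% with 168 randomised. With partial data kept in the model, these completer-based values are cautious planning figures. Alternatively, say that 168 means completers.
3. Describe the figure as power for the PGWBI group-by-time interaction, not for physical activity.

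The cost is a few sentences and a less favourable power statement. No extra enrolment is needed, and the growth curve model is already in the plan.
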